The calculation was based on an estimated mean difference of 18 points [41] (standard deviation of 24.6) [42] in shoulder disability, assessed with Shoulder Pain and Disability Index (SPADI), with a two-tailed significance set at 0.05, power at 80%, and accounting for a 15% dropout, which resulted in 36 individuals per group for a total of 72 individuals. The sample size, calculated based on pain intensity (a mean difference of 2 points and a standard deviation of 2.5 on the NPRS), resulted in a total sample of 48 individuals. Therefore, the sample size calculation for this study was based on shoulder disability.

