### Randomization

Participants will be randomly assigned (1:1 ratio) to the CFT or Therapeutic Exercises groups (Fig 1). An independent researcher will carry out the randomization using a computer-generated sequence from http://www.randomization.com, stratified by age (<or ≥ 50 years) and sex (female or male), with group assignments concealed in consecutively numbered, sealed, opaque envelopes. These envelopes will be securely stored and opened sequentially by an independent researcher before the first session, ensuring allocation concealment.

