### Procedures

Baseline assessments will include the characteristics of the participants, such as sociodemographic data (e.g., sex of birth, age, height, weight, body mass index, occupation, education level, upper limb dominance, physical activity characteristics) as well as information related to shoulder pain (e.g., painful side, duration of symptoms, pain intensity, use of medication, influence of pain on work, leisure activities, and sleep, and details of previous treatments). The self-reported most painful shoulder will be considered for all outcome measures for individuals with bilateral symptoms. Outcome measures will be assessed at baseline, 4-week, at the end of treatment (8-week), and 12-week follow-up, except patients’ expectations of treatment, which will be measured only at baseline, and perception of improvement/deterioration, which will be measured at 4-week, 8-week, and 12-week follow-ups (Fig 2). Patients’ treatment expectations will be assessed using the question “How much do you expect your shoulder to improve at the end of treatment?”. The score will be measured on a 7-point Likert scale, where 1 corresponds to “the worst possible” and 7 corresponds to “fully recovered”. This assessment will be conducted before the intervention begins. Patient expectations are a significant predictor of treatment outcomes, as demonstrated by a study evaluating individuals with shoulder pain [43].

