### Data analysis

Statistical analysis will be conducted using the Statistical Package for the Social Sciences (SPSS) version 24.0 or a more recent version (SPSS Inc., Chicago, IL). Continuous data will be summarized as means ± standard deviation (SD) and 95% confidence intervals (CIs). Data normality will be assessed through visual inspection of histograms and the Shapiro-Wilk test. The analysis will adhere to the intention-to-treat principle. Between-group differences (treatment effects) and their corresponding 95% CIs will be computed using linear mixed models with Bonferroni adjustments. If non-normality of the data is identified, transformations will be performed as needed or generalized linear mixed models will be considered. Fixed effects will include group, time, and the group-by-time interaction. Random effects will account for individual variability. A significance level of 0.05 will be applied for all statistical tests.

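### The listed mixed model adjusts for neither the baseline score nor the two stratification factors, and so gives up precision whichever contrast is reported

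*Protocol article*

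**What the plan says.** The Data analysis section says that treatment effects are between-group differences with 95% confidence intervals from linear mixed models. It lists the terms: "Fixed effects will include group, time, and the group-by-time interaction". On the random part it says: "Random effects will account for individual variability". No covariate is listed there, and no other section adds one.

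The Randomization section says that allocation is 1:1 and "stratified by age (<or ≥ 50 years) and sex (female or male"). It mentions no blocking within strata.

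The Procedures section gives the visits: "Outcome measures will be assessed at baseline, 4-week, at the end of treatment (8-week), and 12-week follow-up". Both primary outcomes, NPRS and SPADI, therefore have a baseline value. The Global Rating of Change starts at week 4 and has none.

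The article does not say whether baseline is one level of time in the model. It also does not say whether the treatment effect is the difference at a visit or the difference in change from baseline.

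The sample size rests on an "estimated mean difference of 18 points [41] (standard deviation of 24.6) [42] in shoulder disability". The other inputs are a two-sided alpha of 0.05, 80% power and an allowance of 15% for dropout. The article arrives at 36 per arm, 72 in all.

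**The concern.** A trial of 72 people has little precision to spare. The baseline value of the same scale is usually among the stronger predictors of the follow-up value, and adjusting for it costs nothing once it has been measured. The listed model does not do so. If baseline is one level of time, the arms are free to differ at baseline, and the baseline score does not serve as a covariate. If baseline is left out of the outcome vector, it is not used at all.

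The second gap is that allocation is stratified on two factors that the analysis then ignores. If those factors predict outcome and are balanced between arms by design, a model without them overstates the standard error of a difference at a visit.

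At stake are the width of the primary confidence intervals and the chance of detecting the planned difference. Validity is not at stake.

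**Working it through.** **Inputs from the article (Sample section).** SPADI difference 18, SD 24.6, two-sided alpha 0.05, power 80%, dropout 15%, 1:1 allocation.

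**Assumed, because the article does not give them.** The baseline-to-follow-up correlation ρ, shown from 0.3 to 0.6; the share R² of outcome variance explained by age and sex, shown at 5% and 10%; and an SD of 24.6 at baseline as well as at follow-up.

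**Step 1: reproduce the plan's figure.** With equal arms the article's formula reduces to n = 2(1.960 + 0.842)² × 24.6² / 18² = 29.3, so 30 per arm. Dropout: 30 / 0.85 = 35.3, so 36 per arm and 72 in total. This matches. The formula is an unadjusted comparison of two means, so the planned power does not depend on baseline adjustment.

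**Step 2: standard error under each contrast, 30 completers per arm, complete data.** In each case SE = 24.6 × √(2v/30), where v is the per-arm variance relative to SD²:
- difference at a visit: v = 1, so SE = 24.6 × √(2/30) = 6.35;
- difference in change from baseline (the group-by-time contrast): v = 2(1 − ρ);
- baseline as covariate, or a common baseline mean: v = 1 − ρ².

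Power is from the noncentral t distribution with 58 degrees of freedom.

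| ρ (assumed) | At a visit: SE, power | Change: SE, power | Baseline-adjusted: SE, power |
|---|---|---|---|
| 0.3 | 6.35, 80% | 7.52, 65% | 6.06, 83% |
| 0.4 | 6.35, 80% | 6.96, 72% | 5.82, 86% |
| 0.5 | 6.35, 80% | 6.35, 80% | 5.50, 90% |
| 0.6 | 6.35, 80% | 5.68, 88% | 5.08, 94% |

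The entry of 80% is 79.6% before rounding. The normal formula used for planning gives 80.9% at 30 per arm.

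The adjusted analysis is never less precise than either alternative: 1 − ρ² ≤ 1, and 2(1 − ρ) − (1 − ρ²) = (1 − ρ)² ≥ 0. Against the difference at a visit, the standard error falls by 5% at ρ = 0.3 (√0.91 = 0.954) and by 20% at ρ = 0.6 (√0.64 = 0.80).

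**Step 3: omitted strata, difference at a visit.** If age and sex are balanced between arms, the reported standard error is too large by the factor 1/√(1 − R²), and the true type I error is 2[1 − Φ(1.96/√(1 − R²))]:
- R² = 5%: interval 2.6% too wide, type I error 4.4%;
- R² = 10%: interval 5.4% too wide, type I error 3.9%.

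A simulation with 60 completers, four strata, an assumed block size of 4 within strata and 4,000 replicates gave 4.5% and 3.8%.

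**Step 4: omitted strata, difference in change.** A stratum effect that is equal at all visits cancels when baseline is subtracted. The same simulation, with R² from 5% to 20%, gave type I error of 4.7% to 4.9%, so there is essentially no mismatch.

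**The case against.** The strongest reply is that nothing here is an error. The 72 was derived without adjustment, so for a difference at a visit the trial has about the power it claims, and adjustment would be a bonus. That stands: for this contrast the loss is a forgone gain. It does not carry over to a difference in change, where power falls short of plan if ρ is below 0.5.

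A second reply is that a condensed article may leave covariates to an analysis plan. This would settle the matter if the article were silent, but it lists the fixed effects, and the list is at odds with the stratified design. It is fair, however, that the article never calls baseline a level of time. That is the natural inference from the visit schedule, not a stated fact. The precision argument does not depend on it, because the baseline score is not a covariate on either reading.

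A reader might go further and infer that chance baseline imbalance passes straight into the estimate, or that the confidence intervals are wrong for the stratified design. The article supports neither as a general statement:
- A change contrast subtracts the baseline value. With missing visits, a likelihood-based mixed model also borrows from each person's observed visits, so even the contrast at a visit is not simply the raw difference in means.
- The interval mismatch is conservative and small, and it applies only to a difference at a visit. It needs strata that predict outcome, for which the article gives no evidence, and balance within strata, which unblocked allocation would not force.

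Finally, the entry thresholds for pain and disability restrict the baseline range and may lower ρ. That favours the low end of the table, where adjustment gains least over a difference at a visit (80% to 83%) but most over a difference in change (65% to 83%).

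**Conclusion.** The point holds as one of efficiency. The listed model uses neither the baseline score as a covariate nor the stratification factors. With 30 completers per arm and an assumed correlation of 0.3 to 0.6, baseline adjustment reduces the standard error for SPADI from 6.35 to between 6.06 and 5.08 if the effect is a difference at a visit. If it is a difference in change, the reduction is from between 7.52 and 5.68 to the same adjusted values. Only the change contrast with a correlation below 0.5 puts power under the planned 80%.

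The strata are the lesser part: intervals about 3% to 5% too wide for a difference at a visit, if age and sex explain 5% to 10% of variance and are balanced within strata, and almost nothing for a change contrast. There is no bias and no inflated type I error. The sizes rest on correlations and variance shares that the article does not give, on equal SDs at baseline and follow-up, and on complete data among 30 per arm. The direction of the baseline result holds for any positive correlation below 1. The change should be made, but the trial would remain valid without it.

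**What to change.** Model the scores at weeks 4, 8 and 12 with fixed effects for group, visit, group-by-visit, baseline score, baseline-by-visit, age stratum (below 50, 50 or over) and sex, keeping the within-person random part. A close alternative keeps baseline in the outcome vector and constrains the arms to a common baseline mean, with the strata added. The two are not identical when data are missing, so the plan should choose one.

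State that the treatment effect is the adjusted between-group difference at a named visit. For the Global Rating of Change, which has no baseline value, adjust for the strata only.

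The cost is wording. All the variables are already collected, and the article places the analysis after the end of data collection, so the model can be fixed before anyone sees results by arm.

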**Methods:**

This will be a randomized controlled trial, single-blinded with two parallel groups. Seventy-two individuals with chronic shoulder pain will be randomly assigned to one of two groups: CFT or Therapeutic exercise. The interventions will last 8 weeks, with the CFT group receiving therapy once a week and the therapeutic exercise group receiving sessions twice a week. The primary outcomes will be pain intensity and disability, while the secondary outcomes will include function, self-efficacy, sleep quality, biopsychosocial factors, perception of improvement/deterioration, and central pain processing. The outcome measures will be assessed at baseline, 4^th^ week, end of treatment (8^th^ week), and 12^th^-week follow-up.

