### Primary outcomes

#### Numerical Pain Rating Scale (NPRS).

The 11-point NPRS will measure shoulder pain intensity during functional activity involving arm elevation and the highest pain intensity experienced in the past week. The scale ranges from 0 (no pain) to 10 (maximum pain) and is a valid and reliable tool for assessing individuals with shoulder pain (intraclass correlation coefficient - ICC of 0.84) [42,44]. The minimum clinically significant difference (MCID) is a change of 2 points or 30% [45].

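### No primary visit, NPRS reading, success rule or Bonferroni family is fixed, so if any primary contrast may win, the 5% error rate and 80% power cannot both hold

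*Protocol article*

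**What the plan says.** - Outcomes: the abstract states "The primary outcomes will be pain intensity and disability". Table 2 lists the NPRS and the SPADI as the two primary measures.
- NPRS: its subsection under Primary outcomes says "The 11-point NPRS will measure shoulder pain intensity during functional activity involving arm elevation and the highest pain intensity experienced in the past week". These are two readings, and neither is named as the primary one.
- Visits: the Procedures section says "Outcome measures will be assessed at baseline, 4-week, at the end of treatment (8-week), and 12-week follow-up". That makes three post-baseline comparisons, with none named as primary.
- Model: under Data analysis, between-group differences and their confidence intervals "will be computed using linear mixed models with Bonferroni adjustments". "Fixed effects will include group, time, and the group-by-time interaction". The same paragraph ends with "A significance level of 0.05 will be applied for all statistical tests".
- Sample size: the Sample section says "The calculation was based on an estimated mean difference of 18 points" on the SPADI. It uses SD 24.6, two-tailed 0.05, 80% power and 15% dropout, giving 36 per group. The 0.05 is not divided for any multiplicity. The Strengths and limitations section claims adequate power for every outcome.

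**The concern.** SPADI plus one NPRS reading at three visits gives 6 between-group contrasts; with both readings there are 9. Nothing says which contrast decides the trial, or whether superiority needs one outcome or both.

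The only multiplicity control is a Bonferroni adjustment whose family is undefined. A mixed model is fitted to one outcome at a time, so on the natural reading the adjustment cannot reach across SPADI and NPRS. With two arms there is a single between-group contrast per visit, so a correction for pairwise group comparisons within a visit would change nothing.

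At stake are the meaning of a positive result and the freedom to choose the visit or the NPRS reading after seeing the data.

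**Working it through.** **1. Reproduce the sample size.** Inputs from the Sample section: d = 18, SD = 24.6, two-sided 0.05, power 80%, ratio 1:1, dropout 15%.

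n per group = 2 × (1.960 + 0.842)² × 24.6² / 18² = 29.3, rounded up to 30. With dropout, 30 / 0.85 = 35.3, rounded up to 36. The total is 72, as stated. The calculation therefore allows for one SPADI comparison at an unadjusted 0.05.

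**2. Family-wise error if any one contrast may win.** With k independent tests at 0.05 the error is 1 − 0.95^k:
- k = 6: 26.5%
- k = 9: 37.0%

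The contrasts are correlated, and the article gives no correlations. I assumed 0.4-0.8 between outcomes (including between the two NPRS readings) and 0.5-0.7 between visits. The correlation of two contrasts differing in both is the product. Correlated normal test statistics were simulated under no treatment effect, counting how often the largest exceeded the critical value.

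| What Bonferroni covers | Level per test | SPADI + one NPRS reading (6) | SPADI + both readings (9) |
|---|---|---|---|
| None of these contrasts | 0.05 | 17-23% | 20-31% |
| The three visits within each outcome | 0.05/3 = 0.0167 | 6-8% | 8-12% |
| All primary contrasts | 0.05/6 or 0.05/9 | 3-4% | 3-4% |

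With independence the middle row is 1 − (1 − 0.0167)^6 = 9.6% and 1 − (1 − 0.0167)^9 = 14.0%.

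**3. Power when the adjustment is wide enough.** With 30 completers per group, the standardised SPADI difference is 18 / (24.6 × √(2/30)) = 2.834. Normal-approximation power is Φ(2.834 − z), where z is the two-sided critical value. The t-based figure is exact for a two-sample t test.

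| Level | z | Normal | t-based |
|---|---|---|---|
| 0.05 | 1.960 | 81% | 80% |
| 0.0167 | 2.394 | 67% | 64% |
| 0.05/6 = 0.0083 | 2.638 | 58% | 54% |
| 0.05/9 = 0.0056 | 2.773 | 52% | 49% |

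Restoring 80% power at the last two levels by the plan's own formula needs 46 and 49 completers per group. After dropout that is 46 / 0.85, so 55 per group (110 in total), or 49 / 0.85, so 58 per group (116 in total), against the planned 72.

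**4. Naming a visit is not enough by itself.** With one fixed visit, but a win allowed on either outcome at 0.05, the error under the same assumptions is about 8-9% with one NPRS reading and about 10-13% with both.

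**The case against.** The strongest reply is that the plan does correct for multiplicity. Bonferroni is attached to exactly the between-group effects at issue, and the 0.05 may be the level applied to adjusted p-values. That stands. A reader might infer from the 0.05 sentence that every primary contrast is tested unadjusted, so that the false-positive rate is simply 17-31%. The document does not support that: this range is the least favourable of three readings, and it also needs a win-on-any rule that the article never states.

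Other parts of the reply also stand:
- If both outcomes had to succeed at one fixed visit, there would be no inflation.
- If the group-by-time interaction were the deciding test, there would be one test per measure: 1 − 0.95² = 9.75% for two independent tests, less if correlated.
- Table 2 shows the NPRS as one measure, so the count of 9 depends on both readings being tested separately.
- The correlations are assumptions.

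It can also be said that a SAP commonly fixes the adjustment family and the testing order. That is fair for the fine detail. It does not answer the inconsistency in what the article does fix. The per-model reading exceeds 5% under a win-on-any rule, and the reading that restores 5% conflicts with a sample size set at an unadjusted 0.05. The primary visit and the primary measure also define the trial's question, which belongs in the protocol.

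**Conclusion.** The point holds as one of undefined error control and a conflict with the stated power. It does not show that error is uncontrolled.

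If any primary contrast may support superiority, the family-wise error is about 6-12% when Bonferroni covers the visits within each outcome, and about 17-31% when it reaches none of these contrasts (up to 37% if they were independent). Only a Bonferroni family of all 6 to 9 contrasts keeps it at or below 5%, and SPADI power then drops from about 80% to about 49-54%. Under that rule the stated error rate and the stated power cannot both hold.

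The error rates rest on the assumed correlations and the win-on-any rule. The power figures rest on the plan's own difference and SD, 30 completers per group and a two-sample t test at one visit; a mixed model using baseline and repeated measures could do somewhat better. The missing visit, reading and success rule rest on the text alone.

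**What to change.** Before any outcome is compared by group:

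1. Name one primary visit, for example week 8, the end of treatment.
2. Name one primary NPRS reading, for example worst pain in the past week, which matches the recall period of the eligibility criterion.
3. Test in fixed order: SPADI at that visit at two-sided 0.05, then the named NPRS reading at 0.05 only if SPADI is significant.
4. Make the other visits and the other NPRS reading secondary, reported with 95% confidence intervals.
5. State which comparisons the Bonferroni adjustment covers.

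This holds the family-wise error at 5%. It leaves the SPADI calculation, and so the target of 72, valid as written. An explicit both-outcomes rule at one visit would also control error, but its power would have to be checked.

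The cost is a few sentences in the protocol, SAP and registry entry, by the amendment route the article already describes, with no extra patients. The downside is that no confirmatory claim on pain can be made if SPADI is not significant.

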### Data monitoring

Monitoring will be conducted by a researcher independent of the trial investigators, to ensure data integrity and trial compliance. No interim analyses or stopping are planned for this study. The analysis will be conducted after the completion of all recruitment and data collection.

### Harms

Adverse events and unintended effects will be collected and reported throughout the trial and to the Human Research Ethics Committee of the Universidade Federal da Paraíba. Individuals will be asked to report any side effects, which will be analyzed by the research team. All adverse events will be evaluated by their severity and potential relation to the interventions. The use of pain relief methods, such as medication, ice, or heat packs, during the study period will also be recorded.

### Auditing

An independent researcher will review the study’s progress, audit the quality and completeness of the data every six months, and ensure that all protocol procedures are being implemented as planned.

## Ethics and dissemination

### Research ethics approval

This trial protocol was approved by the Research Ethics Committee at Universidade Federal da Paraíba (CAAE: 84462524.8.0000.5188). Any changes made to the research protocol will be submitted to the Research Ethics Committee and registered on the clinical trial registration platform.

### Protocol amendments

Any protocol amendments will be previously requested to the ethical committee and then informed to all relevant parties, including trial registries and participants.

### Ancillary and post-trial care

No provisions are planned for ancillary or post-trial care. Compensation for any harm related to trial participation will be provided per institutional guidelines.

### Dissemination policy

The trial results will be disseminated through peer-reviewed publications, conference presentations, and public reports. Researchers who make substantial contributions to the study’s design, execution, interpretation, or reporting will be credited as authors in the final publication, and no professional writers will be involved in the manuscript preparation. Access to the full protocol, participant-level dataset, or statistical code will be available upon request.

## Discussion

Rehabilitation for shoulder pain can be prolonged and place a burden on healthcare systems, highlighting the need for more effective treatment solutions. Pain is influenced by biological, psychological, emotional, and social factors, yet standard treatments often overlook psychosocial aspects. CFT is a recent and promising approach for treating various musculoskeletal disorders, but its effectiveness in shoulder pain has not yet been explored. The results of this randomized controlled trial could provide valuable evidence supporting the use of CFT to enhance shoulder pain rehabilitation.

